## Abstract

**Background:**

Alcohol misuse among youth is a major public health concern and numbers of adolescents admitted to the emergency department for acute alcoholic intoxication in Germany are recently growing. The emergency setting offers an opportunity to reach at-risk alcohol consuming adolescents and provide brief interventions in a potential “teachable moment”. However, studies on brief interventions targeting adolescents in emergency care are scarce and little is known about their effectiveness when delivered immediately following hospitalization for acute alcohol intoxication. In this protocol we present the *HaLT-Hamburg* trial evaluating a brief motivational intervention for adolescents treated in the emergency department after an episode of acute alcoholic intoxication.

**Methods:**

The trial design is a parallel two-arm cluster randomized-controlled trial with follow-up assessment after 3 and 6 months. N = 312 participants aged 17 years and younger will be recruited Fridays to Sundays in 6 pediatric clinics over a period of 30 months. Intervention condition is a manual-based brief motivational intervention with a telephone booster after 6 weeks and a manual-guided intervention for caregivers which will be compared to treatment as usual. Primary outcomes are reduction in binge drinking episodes, quantity of alcohol use on a typical drinking day and alcohol-related problems. Secondary outcome is further treatment seeking. Linear mixed models adjusted for baseline differences will be conducted according to intention-to-treat (ITT) and completers (per-protocol) principles to examine intervention effects. We also examine quantitative and qualitative process data on feasibility, intervention delivery, implementation and receipt from intervention providers, receivers and regular emergency department staff.

**Discussion:**

The study has a number of strengths. First, a rigorous evaluation of *HaLT-Hamburg* is timely because variations of the *HaLT* project are widely used in Germany. Second, prior research has not targeted adolescents in the presumed teachable moment following acute alcohol intoxication. Third, we included a comprehensive process evaluation to raise external validity. Fourth, the study involved important stakeholders from the start to set up organizational structures for implementation and maintaining project impact.

**Trial registration:**

Current Controlled Trials ISRCTN31234060 (April 30^th^ 2012).

## Background

Alcohol misuse and particularly episodic heavy drinking is a significant public health concern across contemporary societies [1]. In 2011, 47% of European students aged 15 to 16 years experienced alcohol intoxication at least once in their lifetime and 17% did so during the last month [2]. In Germany, the number of adolescents admitted to in-patient treatment for acute alcoholic intoxication (AAI) is recently growing. During the last years the number has more than doubled to over 26.000 in 2011 [3], with high rates of repeated episodes of alcohol intoxication if not treated adequately [4].

Personal health risks associated with AAI for adolescents have been widely documented, including aggressive [5,6] and risky sexual behavior [7] and elevated mortality rates through injury [8] and traffic accidents [9]. Moreover, heavy episodic drinking in adolescence is associated with a number of social and developmental problems, such as deleterious effects on neurocognitive and hormonal development [10-12] and cognitive and emotional abilities [13-15]. Social conflicts, delinquency and problems of academic adjustment are often associated with repeated episodes of heavy drinking [16,17] also puts youth at risk for chronification of problematic substance use patterns into adulthood [18,19]. Beyond these immense personal risks, alcohol-related problems also impose significant economic burdens on public health care [20]. Thus, excessive alcohol use in adolescents continues to be a major public health problem [21,22] and indicated preventive interventions as early as in adolescence are essential [23,24].

### Current evidence for brief alcohol interventions

To date, brief interventions (BI’s) are among the most empirically supported individual level interventions for reducing alcohol use and alcohol-related problems in adolescents [25,26]. They are often based on principles of Motivational Interviewing (MI) [27], which is characterized by an empathic approach to the client and a non-judgemental and non-confrontative counseling style [28]. Such short-term preventive or therapeutic interventions usually span one to three sessions [29,30] with the goal to establish and support intrinsic motivation for behavior change and/or further treatment seeking [31]. A comprehensive body of evidence documents the usefulness of BI’s for problematic alcohol use in primary care [32] and general hospitals [29]. The emergency department (ED) has been identified as a feasible setting to implement early interventions for problematic alcohol use [33,34] and efficacy of BI’s in ED has attracted a substantial body of research [35-37]. However, with few exceptions [4,38-41] to date adolescents have been only sparsely addressed [42,43]. None the less a small number of studies indicate feasibility and effectiveness of BI’s for adolescents in an ED following an *alcohol-related event* such as alcohol-induced injury [38-40]. While these studies vary substantially in key conceptual and methodological issues and the heterogeneity of findings limits generalization [[name], [name], [name], [name]: *Brief Interventions for Alcohol-involved Adolescents in Emergency Care: A Systematic Review,* forthcoming] [43], these studies are informative because they support the notion that alcohol-related events causing hospitalization are associated with a “teachable moment” that opens a window of opportunity for effective intervention [44-46]. The experience of a potentially life-threatening AAI resulting in hospitalization supposedly leaves adolescents in a state of increased responsiveness to alcohol-related counseling [46,47]. While awareness of alcohol having prompted ED hospitalization generally influences BI outcomes [45], there is currently a lack of studies addressing the potentials of BI’s following AAI hospitalization. Given the articulated need for indicated preventive interventions for AAI we build on the current empirical and conceptual base for BI’s in this context as well as our own favourable pilot results for feasibility and initial effectiveness in this context [4]. In this study protocol we present the design and current implementation of a randomized-controlled trial that aims at evaluating effectiveness of a manualized brief motivational intervention (BMI) (indicated intervention) for children and adolescents who are being treated in the ED immediately following AAI, an approach that has been established in Germany and other European countries [48-50] over the last 10 years (see below) but has not been rigorously tested to date. Moreover, we include additional evaluative components to address practical conditions within the “real-world” ED-setting that might affect effectiveness and implementation [51,52].

### *HaLT-Hart am LimiT* (“Stop – close to the limit”)

*HaLT*[53] is a German alcohol prevention project that involves a broad network of cooperating institutions to pursue the goal of early prevention of heavy alcohol use among children and adolescents [54]. It is one of the most broadly applied alcohol-specific prevention projects for under 18 year-olds and is currently implemented in more than 160 locations across Germany. It was initiated against the background of growing numbers of children and adolescents in need of emergency medical care following an episode of AAI and growing evidence that adolescents with at-risk alcohol consumption can best be reached in the ED setting [55]. *HaLT* involves two strategies. First, a *proactive* or structural prevention component which aims at promoting responsible alcohol use through outreach work in schools, informing festival organizers and pub owners about risks of underage drinking and providing support for correct implementation of alcohol-specific regulations for the protection of minors. Second, a behavior-oriented or *reactive* component which includes an individual level “bridging session” targeting children and adolescents in the ED following an AAI and a brief consultation for their caregivers. The reactive component is topic to the study presented in this protocol. The “bridging session” is a single-session, semi-structured indicated preventive intervention based on core principles of MI and implemented by trained facilitators before discharge from hospital. Facilitators provide information on risks associated with excessive drinking and strategies for reducing these risks while highlighting personal responsibility for behavior change. They aim at raising awareness for consequences of risky alcohol consumption and establishing a positive relationship in order to motivate adolescents to take part in an experience-oriented group-training (*risk-check*) for risk-related competences which is offered by a cooperating counseling agency as part of the *HaLT* project (not further addressed in this protocol). Parents or caregivers are also adressed in hospital in order to enhance their motivation to support their child in participating in the group-training. To date, *HaLT* services have been partly evaluated but not using rigorous evaluation methods (RCT). Moreover, existing results [54,56-58] are difficult to generalize because in the field *HaLT* is practically implemented in a broad spectrum of modulations and lacks standardized procedures in intervention content and delivery. The *HaLT-Hamburg* intervention, which is subject of the trial presented in this protocol, includes a number of further developments when compared with *HaLT*. First, a theory-based manualized BMI including a counseling session with caregivers. Second, a manualized training for facilitators in delivering the *HaLT-Hamburg* BMI. Third, definition of standards regarding qualification of facilitators. Fourth, regular clinical group supervision for facilitators and fifth, a pragmatic manual adherence monitoring. Internationally, to our knowledge we are the first to evaluate effectiveness of a BMI for adolescents admitted for AAI in the ED using a randomized-controlled design.

### Objectives and hypotheses

The objective of this study is to evaluate the effectiveness of a manual-based BMI for adolescents admitted for AAI in the ED. Effectiveness will be evaluated by expected reductions of binge-drinking frequency (5 or more standard drinks at one occasion (4 for female) [59]), quantity of alcohol consumption on a typical drinking day and alcohol related problems at 3 and 6 month follow-up. Our primary hypothesis is that children and adolescents under the age of 18 years who receive the manualized BMI following AAI hospitalization will show lower levels on these outcomes when compared to controls not receiveing this treatment. We also include further health care utilization in response to the BMI as secondary outcome. Help seeking in the care system as recommended in our BMI is closely related to intention to change [60] and appropriate for additionally judging intervention effectiveness. We thus hypothesize that children and adolescents who receive the BMI will significantly more often access further counseling regarding alcohol use in the 6 months following hospitalization than children and adolescents who do not receive the BMI. Moreover, we will examine a number of expected moderating variables such as psychopathological symptoms, drinking history, concurrent substance use and family environment. Finally, alongside our RCT we include additional evaluation components that focus on process, context and practical implications for BMI delivery under “routine conditions” in the ED setting.

## Methods

### Trial design, setting and time frame

The *HaLT-Hamburg* study is a parallel two-arm (intervention and control) stratified cluster RCT with follow-up assessments at 3 and 6 months post intervention with hospital on a weekend as unit of randomization and weekend as stratum. All participants receive standard inpatient ED care for AAI. Participants in the intervention group additionally receive a single session manualized BMI before ED discharge with one telephone booster session 6 weeks after the BMI. Caregivers of adolescents in the intervention group also receive a short manual-guided intervention by the same facilitator that delivered the BMI to the adolescent. Participants in the control group receive treatment as usual (TAU) only which is written information on negative consequences of alcohol use in adolescence and information on youth specific substance use counseling agencies. Recruitment of hospitals started in February 2011. Participant data collection started in July 2011 and lasts 30 months with final follow-up assessments being planned for July 2014. Figure 1 displays the CONSORT flow diagram of the study design.

**Figure 1 F1:**
[figure not shown]
CONSORT flow diagram with anticipated case numbers.

#### Participating hospitals

ED directors of six pediatric hospitals identified as main treatment providers for alcohol-intoxicated adolescents under the age of 18 [61] in the City of Hamburg, Germany, were invited to a network conference at project launch, informed about the aims and procedures of the project and asked to participate. The conference was hosted by the Hamburg authorities for Health and Consumer Safety (BGV) who cooperates closely in project implementation. It was made clear that BMI’s will be delivered by external trained facilitators funded by health insurers since high workload and limited resources by ED staff are widely perceived as barriers for implementation in this context [34]. All six clinics spanning the area of the city agreed to participate in the study. In order to reach as many eligibles as possible the BGV issued an instruction for the Hamburg rescue coordination center to transfer adolescents with AAI to the six participating ED’s.

### Participants

#### **
*Eligibility*
**

Study participants are children and adolescents admitted for AAI (diagnosis F10.0; ICD 10; [62]) in one of the participating clinics and their caregivers. They are eligible for participation if they fulfill the following inclusion criteria: 1. at hospitalization they are under the age of 18 years, 2. at time of data collection and intervention delivery they have sufficiently recovered from AAI and show sufficient mental-cognitive receptiveness, 3. they are fluent in German, 4. informed consent is given by participant and parent(s)/caregiver(s), 5. absence of severe injuries. We have purposefully limited exclusion criteria and designed inclusion/exclusion criteria for study participation to reflect actual clinical conditions. In principle, all individuals that would receive the BMI under “real” clinical conditions are eligible to participate in the study. This way we aim at maximizing external validity of our study findings. The age limit reflects the age range adressed in the German-wide *HaLT* project.

#### **
*Recruitment and procedure*
**

Given that previous studies indicate that in Germany most AAI’s in youth happen at Friday and Saturday night [61], and an everyday stand-by recruitment was not possible due to limited resources, we recruit participants in the participating clinics on Friday, Saturday and Sunday mornings (between 7 – 9 am). Recruitment and data collection is carried out by trained research assistants and intervention delivery by trained facilitators who form a mobile intervention team. Coordination of attendance and resource availability is managed by a detailed operation schedule for each weekend. At each weekend in the evaluation period, research assistants contact all participating hospitals and ask about under 18 year-olds admitted to ED following AAI. If this is the case and if the patient has not been discharged in the same night, a research assistant visits the patient in hospital, informs about the project (evaluation and intervention), confidentiality, voluntariness of participation and right to withdraw consent and obtains active informed consent to participate in the study from patients and caregivers. Patients in the intervention and the control group are informed that they are compensated with incentives (shopping vouchers) summing up to €60 for complete data collection (€10 for baseline assessment and €25 for each completed follow-up assessment). If eligible patients and their caregivers who are willing to give consent are hospitalized in a clinic that was randomly assigned to form the intervention group for this weekend, the research assistant contacts one of the facilitators to deliver the BMI. Adolescents in the intervention group are contacted by telephone 6 weeks after hospitalization for a 5–10 minute manualized booster session to enhance motivation to pursue alcohol-related goals as set in hospital. All study participants are assessed via telephone for follow-up at 3 and 6 months post intervention. Approval for the study was obtained from the ethics committee of the Chamber of Psychotherapists Hamburg (Germany) prior to data collection. The study is conducted in accordance with CONSORT guidelines (Additional file 1) and is registered under Current Controlled Trials ISRCTN31234060 (http://www.controlled-trials.com/ISRCTN31234060).

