### BMI condition

#### **
*HaLT-Hamburg brief intervention*
**

The BMI is based on the German prevention program “*HaLT-Hart am Limit*” (“*Stop – close to the limit*”) and was adapted in a participatory process with cooperating practice partners, a youth-specific substance use counseling agency and an outpatient clinic for adolescents and young adults with substance use disorders. It is based on MI [28] and components reflect BMI elements as put forward by Spirito et al. [38]. The intervention is manual-based and consists of one 45-minute session. It’s 5 components are: 1. Introduction to the session with positive feedback on patient’s willingness to engage in the intervention, expression of interest and concern transporting a positive and empathic therapeutic mindset and explanation of the intervention’s aim and content. 2. A semi-structured interview assessing circumstances of the intoxication and alcohol-related risk behaviors. 3. Exploration phase incorporating discussion of motivation to drink, normative feedback, exploring pros and cons of current alcohol use, optional use of MI tools (i.e., importance and confidence ruler, decisional balance sheet) and establishment of future scenarios with changed/unchanged alcohol use. 4. Summary in which the facilitator structures and sums up what has been discussed, highlights personal responsibility for change and asks the patient for his/her conclusion from what has been discussed so far. 5. Closure of the session beginning with identification of drinking goals and potential barriers and development of strategies for goal attainment. The session is finished with a written agreement on drinking goals, the introduction of the cooperating youth-specific counseling agency and promotion of patient’s self-efficacy.

#### **
*Counseling session for caregivers*
**

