### Control condition

Participants in the control group are approached by a research assistant. After informed consent is given, they receive TAU which presently consists of oral and written information on cooperating youth- and family-orientated counseling agencies combined with the recommendation to contact a counseling agency and a flash drive with information on negative consequences of alcohol misuse for children and adolescents. Personal contact for TAU has a duration of 5–10 minutes.

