### Statistical analysis

Basic descriptive statistics will be calculated for baseline variables, and according to trial arm (BMI vs. control). Intention-to-treat (ITT) analysis will be based on available data from all randomized patients at 3 and 6 month follow-up. In case of missing follow-up values multiple imputation will be performed [85]. For primary and secondary hypotheses we will use linear mixed models adjusted for baseline differences to examine differences between intervention and control group with intervention condition as fixed effect and clusters (hospital on a weekend) as random effect. The two-sided ?-level is set to 0.05. Additional analysis will be conducted on a per-protocol analysis set. Process data on intervention delivery, implementation and receipt will be analyzed in subsequent steps.

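### Inclusion criterion 2 must also hold at intervention delivery, which only the BMI arm has; the eligibility wording should be reconciled with the recruitment, feasibility and ITT text

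*Protocol article*

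**What the plan says.** All places are in the Methods of the protocol article.

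- **Participants, Eligibility.** One list of criteria serves both arms: "They are eligible for participation if they fulfill the following inclusion criteria". Criterion 2 reads "at time of data collection and intervention delivery they have sufficiently recovered from AAI and show sufficient mental-cognitive receptiveness".
- **Participants, Recruitment and procedure.** The two acts named in criterion 2 belong to different people: "Recruitment and data collection is carried out by trained research assistants and intervention delivery by trained facilitators who form a mobile intervention team". The order of events is given as "If eligible patients and their caregivers who are willing to give consent are hospitalized in a clinic that was randomly assigned" to BMI for that weekend, and then "the research assistant contacts one of the facilitators to deliver the BMI".
- **BMI condition.** "The intervention is manual-based and consists of one 45-minute session".
- **Control condition.** Controls are seen by a research assistant only. "Personal contact for TAU has a duration of 5–10 minutes".
- **Additional components of evaluation, Feasibility.** One of the two targets is that at least 90% of participants complete the intervention before they leave hospital.
- **Randomization.** The unit is the hospital on a given weekend, and the allocation plan was drawn up before data collection began.
- **Statistical analysis.** "Intention-to-treat (ITT) analysis will be based on available data from all randomized patients at 3 and 6 month follow-up". A per-protocol analysis is planned in addition.

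**The concern.** An inclusion criterion should be judged at a point that exists in both arms and, ideally, before allocation can influence it. Criterion 2 names two time points, and only the first is common to both arms. The second comes after the allocation is known and is tied to a 45-minute session that controls do not have.

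Suppose two identical patients consent and complete baseline, and would both be judged not receptive when a facilitator arrives later. Taken at its word, criterion 2 is failed by the one in a BMI hospital. The one in a control hospital is never put to that test and stays in.

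If the rule were applied that way, the trial would have a post-allocation exclusion in one arm only. Recovery and receptiveness may be related to later drinking, so the arms could differ for a reason other than treatment. The completion rate used for feasibility could also rise, because patients who did not receive the session would leave its denominator.

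**Working it through.** No figure in the article is in dispute. The check is a comparison of sections, followed by an illustration of scale.

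**Step 1: which time points exist in each arm**

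| Time point in criterion 2 | BMI arm | Control arm |
|---|---|---|
| Data collection (research assistant) | yes | yes |
| Intervention delivery (facilitator) | yes, after the allocation is acted on | none; a 5–10 minute TAU contact with the research assistant |

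Read literally, the second condition can be failed in one arm only.

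**Step 2: does the ITT sentence rule this out?** Not clearly. Hospital-weekends are randomized, not patients. A patient enters the trial by being found eligible and consenting. Someone declared ineligible at delivery could be regarded as never having entered, and the ITT sentence does not say otherwise.

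**Step 3: does other text point to a single judgement?** Yes. Recruitment and procedure treats patients as eligible before any facilitator is called. The feasibility target presupposes participants who do not complete. Sample size goes from 390 assessed to 312 enrolled through the 80% participation rate alone (0.80 × 390 = 312), with no allowance for a later loss in one arm. None of these states that criterion 2 is judged once, or that a patient not receptive at delivery stays in the analysis.

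**Step 4: scale, under assumed values.** Only the effect size of 0.26, the 156 per group and the design effect of 1.013 come from the article (Sample size). The share removed and its relation to outcome are assumptions.

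*Simple form.* If a share p is removed whose mean outcome is d SD worse than that of the rest, the retained mean shifts by p × d:

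- 0.05 × 0.5 = 0.025 SD; 0.025 / 0.26 = 10%
- 0.10 × 0.5 = 0.05 SD; 0.05 / 0.26 = 19%
- 0.10 × 1.0 = 0.10 SD; 0.10 / 0.26 = 38%

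*Selection form.* If the least recovered share q is removed, and recovery correlates r with outcome (both normal), the shift is r × φ(z_q) / (1 − q). Two-sided type I error with no true effect uses a standard error of √(2 × 1.013 / 156) = 0.114 SD.

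| q removed | Shift for r = 0.1 / 0.3 / 0.5 (SD) | Share of 0.26 | Type I error (nominal 0.05) |
|---|---|---|---|
| 5% | 0.011 / 0.033 / 0.054 | 4% / 13% / 21% | 0.051 / 0.059 / 0.076 |
| 10% | 0.019 / 0.058 / 0.097 | 7% / 22% / 37% | 0.053 / 0.081 / 0.137 |
| 20% | 0.035 / 0.105 / 0.175 | 13% / 40% / 67% | 0.061 / 0.151 / 0.336 |

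The sign of r is unknown, so the shift could go either way. The planned baseline adjustment would absorb the part of it explained by baseline values; neither form allows for that.

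*Feasibility.* Assume that the completion rate is taken over the 156 BMI-arm patients and that 10% of them (about 16) do not receive the session. Completion is then 140 / 156 = 89.7%, just under the 90% target. If those 16 were counted as ineligible, it would be 140 / 140 = 100%.

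**The case against.** The strongest reply is that the article describes no second check. Facilitators have no stated role in eligibility, and no text lets a non-completer be reclassified. Patients are already called eligible when the facilitator is contacted. Criterion 2 can be read as fitness for assessment and for a session, judged once at recruitment in everyone. That fits the article's statement that anyone who would get the BMI in ordinary practice is eligible. Recovery from intoxication normally improves with time, and the session need only take place before discharge, so failures at delivery may be rare. This is also a condensed article: the flow diagram is not shown, and a full protocol may fix the screening procedure.

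Much of this stands. A reader might infer that BMI patients are re-screened by the facilitator, that eligibility in fact differs by arm, or that the retained BMI group will look better. The documents support none of these: a re-check is not described, removal is only possible under the wording, and direction and size are unknown.

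What does not fall away is the wording itself. On the milder reading, the reference to intervention delivery either does nothing or asks the research assistant to forecast fitness for a session that only one arm receives. The article states this rule and leaves it at odds with its other sections, so the point does not rest on detail left to a fuller document.

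**Conclusion.** The point holds as a conflict of wording with a possible, unproven consequence. Criterion 2 ties eligibility to an event that occurs only in the BMI arm after allocation. Taken literally it permits removal from one arm, and the ITT sentence does not clearly prevent this because patients are not the unit of randomization. The recruitment order, the feasibility target and the ITT plan suggest that it is not intended.

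The 4–37% of the planned effect for 5–10% removed rests wholly on assumed removal rates and correlations, so it indicates scale and does not estimate bias. With few removals or a weak link to outcome the effect is negligible: type I error is 0.051 at 5% removed and r = 0.1. A change is worth making because it closes the gap at almost no cost.

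**What to change.** Reword criterion 2 so that it is judged once, by the research assistant, at consent and baseline data collection, in the same way in both arms, and drop the reference to intervention delivery.

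Add that every patient enrolled at that point:

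- is followed at 3 and 6 months and analysed as allocated under ITT, whether or not the BMI is started or finished;
- stays in the feasibility denominator, with an undelivered or unfinished session counted as non-completion;
- is affected by non-delivery only through the definition of the per-protocol set.

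If any patients have already been set aside at delivery, report their number by arm in the participant flow.

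The cost is a few sentences. Keeping BMI-arm patients without a session slightly dilutes the ITT effect and may lower the completion rate.
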